### Sample size

We will consider a difference of 0.5 standard deviation, which is equal to a moderate effect size [29], clinically relevant. For calculating the required difference on the Inflammatory Bowel Disease Questionnaire (IBDQ), we will use the data from a study by McColl et al [30] among 111 IBD patients. The mean IBDQ score was 182 and the standard deviation was 59. A 0.5 standard deviation thus equals approximately 30 points on a scale ranging from 32 to 224. With an effect size of 0.5 standard deviation, an alpha level of 0.05, and a power of 80%, at least 34 patients in both the experimental condition and the waiting list control condition are needed. Given a potential attrition rate of 10%, we will include 40 patients in each condition.

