### Statistical analysis

Analyses of covariance will be conducted to determine the extent to which treated patients (experimental condition) show more improvement on the primary and secondary outcome variables compared to patients in the waiting-list control condition. A two-way factorial analysis of variance with the between-factor condition (experimental condition versus waiting list control condition) and the within-factor assessments will be used. Moreover, stratification variables, i.e. gender, treatment center and disease type will be included as covariates in the analyses (ANCOVA).

Additionally, the data of experimental and the waiting-list control condition will be pooled, to measure the overall effect of treatment. Before the two groups will be pooled, we will examine whether there is a difference in effect for the experimental versus the waiting-list control condition (Delta T_follow-up after CBT_-T_baseline before CBT_). In case differences emerge, this will be stratified reported.

For therapy effects, data will be analysed on an intention to treat (ITT) as well as treatment completer basis. The completers sample will include patients who attend at least 5 CBT sessions.

To express the magnitude of the effects, mean gain scores on the outcome measures will be standardized to Cohen’s *d*, representing the number of standard deviations separating the two means. Point estimates and 95% confidence intervals of *d* will be determined for the within and the between group effects. Between effect sizes will be calculated using the pooled standard deviation (of the baseline scores) and confidence intervals will be approximated from the central *t*-distribution.

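### The between-group Cohen's d is built from unadjusted gain scores; a baseline-adjusted difference over the same SD would be more precise at almost no cost

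*Protocol article*

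**What the plan says.** All of this is in the Protocol article, Statistical analysis, unless noted.

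- Numerator of the effect size: "mean gain scores on the outcome measures will be standardized" to Cohen's *d*.
- Denominator: "Between effect sizes will be calculated using the pooled standard deviation (of the baseline scores").
- Interval: 95%, where "confidence intervals will be approximated from the central" *t*-distribution. No standard error is given.
- Comparison of the arms: "Analyses of covariance will be conducted to determine the extent to which treated patients (experimental condition) show more improvement". The next sentence describes the model differently: "A two-way factorial analysis of variance with the between-factor condition" and assessments as the within-factor.
- Covariates: "stratification variables, i.e. gender, treatment center and disease type will be included as covariates in the analyses (ANCOVA"). The baseline value of the outcome is not named.
- Relevance threshold (Sample size): "We will consider a difference of 0.5 standard deviation" clinically relevant.

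No correlation between baseline and follow-up scores appears anywhere in the article.

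**The concern.** The effect size is the quantity that tells readers how large the benefit is, and it is on the same scale as the 0.5 SD that the article calls clinically relevant. As described, it is a plain difference in mean gain. A gain score subtracts the whole baseline value, which amounts to fixing the regression slope of follow-up on baseline at 1. When the true slope is lower, this over-corrects: it adds noise, and it carries part of any chance difference between the arms at baseline into *d*. With about 36 evaluable patients per arm the interval is already about as wide on each side as the threshold itself, so avoidable noise matters for interpretation. The information needed to remove it is collected in every patient before randomisation.

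A second question is whether the interval for *d* has the right width. The usual two-group formula for *d* takes no account of the pre-post correlation, whereas the variance of a gain score depends on it.

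**Working it through.** **Inputs.** 40 patients per arm and 10% attrition (Sample size) give 40 × 0.9 = 36 evaluable per arm, so df = 70 and *t*(0.975, 70) = 1.994. True *d* = 0.5 (Sample size). The pre-post correlation *r* is an assumption: 0.3, 0.5 and 0.7. Baseline and follow-up variances are taken as equal, and variances are in units of the baseline variance. The article gives no figure for the precision of *d*, so there is none to reproduce.

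**Step 1: precision of the numerator.** The gain-score variance is 2(1 − *r*). The variance with baseline as covariate is 1 − *r*². The variance ratio is 2/(1 + *r*), and the SE ratio is its square root.

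| *r* | gain | baseline-adjusted | variance ratio | SE ratio |
|---|---|---|---|---|
| 0.3 | 1.40 | 0.91 | 1.54 | 1.24 |
| 0.5 | 1.00 | 0.75 | 1.33 | 1.15 |
| 0.7 | 0.60 | 0.51 | 1.18 | 1.08 |

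The excess is 2(1 − *r*) − (1 − *r*²) = (1 − *r*)², which is positive for every *r* below 1. If the follow-up SD is *k* times the baseline SD, the excess is (1 + *k*² − 2*rk*) − *k*²(1 − *r*²) = (1 − *rk*)². That is never negative, so the direction does not depend on equal variances.

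**Step 2: chance imbalance.** Given a baseline difference of δ SD between the arms, the expected gain difference is shifted by −(1 − *r*)δ. One standard error of the baseline difference is √(2/36) = 0.236 SD. The resulting shift in *d* is 0.7 × 0.236 = 0.17, 0.5 × 0.236 = 0.12 and 0.3 × 0.236 = 0.07 at *r* = 0.3, 0.5 and 0.7. Over repeated randomisations it averages to zero. It is the source of the excess variance in Step 1.

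**Step 3: 95% half-widths for *d*.** The formula is 1.994 × √(*V* × 2/36 + 0.5²/(2 × 70)). *V* is 2(1 − *r*) for gain scores, 1 − *r*² with baseline adjustment, and 1 in the usual independent-groups formula. Example for gain at *r* = 0.3: √(0.0778 + 0.0018) = 0.282, and × 1.994 = 0.563.

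| *r* | usual formula | gain score | baseline-adjusted |
|---|---|---|---|
| 0.3 | 0.478 | 0.563 | 0.456 |
| 0.5 | 0.478 | 0.478 | 0.416 |
| 0.7 | 0.478 | 0.374 | 0.346 |

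**Step 4: does the interval have the right width?** Simulation of 20,000 trials with 36 per arm and true *d* = 0.5:

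- Usual independent-groups SE applied to the gain-score *d*: coverage 91.2%, 95.4% and 98.7% at *r* = 0.3, 0.5 and 0.7. It is too narrow below 0.5, right at 0.5 and too wide above.
- SE of the gain difference divided by the baseline SD, with central *t*: coverage 94.1% to 95.0% for *r* from 0.3 to 0.8.

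So neither the central *t* nor the baseline SD as denominator is at fault. The width depends on which standard error is put in.

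**The case against.** The strongest case on the other side has four parts.

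**The comparator may not be the planned model.** The article never names the baseline score as a covariate; it names only gender, center and disease type. It also describes a condition-by-assessments analysis of variance, and with two assessments the interaction in that model is itself the comparison of mean gains. A reader might infer that *d* is less precise than the planned ANCOVA, or that effect size and p-value come from different estimators. The text does not establish either. On the factorial reading they share one contrast, and the loss against the planned analysis is only what the stratification factors explain. This part of the objection stands. The loss against an ANCOVA that includes the baseline score remains.

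**The interval may be correct.** A reader might also infer that the planned interval has the wrong width. No standard error is stated, and a gain-based one gives close to nominal coverage. A condensed article may leave that detail to a fuller document. This stands too, so the width problem is only conditional.

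**Gain over baseline SD is a legitimate estimator.** It is unbiased under randomisation apart from small-sample scaling, and its denominator is sensible; the change proposed here keeps it. Agreed: the issue is efficiency.

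**The stakes are modest.** At *r* = 0.7 the half-widths are 0.374 and 0.346, the article sets no decision rule on the interval for *d*, and the test does not depend on it. True, but at *r* = 0.3 the half-widths are 0.563 and 0.456, and the article gives no ground for assuming a high *r*.

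**Conclusion.** The point holds as one about efficiency in effect-size reporting. The article fixes the between-group *d* as an unadjusted gain difference over the pooled baseline SD. Against an ANCOVA with the baseline score as covariate, the SE of the numerator is about 24%, 15% and 8% larger at *r* = 0.3, 0.5 and 0.7, and chance baseline imbalance is left in the estimate. These sizes rest on an assumed *r*, equal variances at the two assessments and 36 evaluable patients per arm; the direction does not need the equal-variance assumption.

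Three stronger conclusions are not supported: that *d* is biased, that it departs from the planned test, and that its interval is wrong. The first fails because of randomisation, the second because the model description is ambiguous, and the third because no standard error is stated. The validity of the primary test is not affected.

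**What to change.** Define the between-group *d*, for the primary and secondary outcomes, as the ANCOVA-adjusted difference between the arms, with the baseline score of that outcome and the stratification factors in the model, divided by the pooled baseline SD. Obtain the 95% CI by dividing that model's confidence limits by the same SD, or by bootstrap if the sampling error of the SD is to be included. This replaces the gain-score version of the between-group *d*; the within-group effect sizes can stay as they are. Naming the model in this way also settles which standard error enters the interval.

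The cost is about one sentence of analysis wording and no new data. The small downside is less direct comparability with reviews that use gain-score *d*.

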#### Effect of CBT on quality of life mediated by cognitions, attitudes and coping

We will subsequently examine the extent to which changes in quality of life will be mediated by improvements in illness-cognitions, attitudes and coping styles and whether this change is associated with outcome.

## Discussion

Given its chronic nature and frequently reported poor quality of life for many patients, IBD is often associated with anxiety and depression. Apart from medical treatment, psychological intervention might be a crucial component of treatment of IBD patients and is needed alongside medical treatment [8,9]. Results from a recent meta-analysis of psychological interventions for treatment of IBD showed that current psychological treatment is not effective among IBD patients [15]. These disappointing results can, however, be attributed to specific treatment programs and a number of methodological short-comings of the evaluation studies. Therefore a further and more stringent study of psychological interventions in IBD patients to enhance quality of life and reduce anxiety and depression is warranted.

A number of strengths of the current study merit attention. First, it will offer a cognitive behavioral treatment manual, which is specifically tailored to the needs of IBD patients. Due to the focus on specific worries and needs of IBD patients, this treatment may be effective in enhancing quality of life and alleviating psychological symptoms, such as anxiety and depression associated with IBD. Additionally, this trial will allow us to investigate and learn more about the mechanisms of CBT. Particularly, illness-related cognitions, dysfunctional attitudes and coping behaviors (i.e. problem solving and avoidance) will be examined in order to understand the most effective components of CBT.

Second, only patients with a poor level of mental quality of life will be included. These patients are the ones who are most in need of psychological help. To the best of our knowledge, no study has previously selected patients based on their initial well-being. However, Larsson et. al. included their patients on another aspect of mental well-being, i.e. anxiety and depressive symptoms (patients with a high HADS anxiety levels) [16]. In this study an education program was employed instead of CBT, potentially explaining the lack of effect in the preselected patient group.

A third strength of the current study will be the random assignment of patients to the experimental group and the waiting list control group. To ensure an equal distribution among these two groups patients will be stratified by gender, treatment center and disease type. These factors are selected for several reasons. First, previous research found that disease course may differ for female and male patients. Particularly, females possibly have a higher risk of disease activity relapse than males [48]. Females, therefore, may have more psychological symptoms. Second, patients will be stratified by treatment center. A distinction will be made between an academic setting and a peripheral setting. We expect that an academic hospital would treat more severe cases of IBD than a peripheral setting. Finally, disease type is also used as a stratification factor. Previous research has found that CD patients undergo more surgical interventions and experience more disease exacerbations than UC patients [49]. This indicates that CD is a more complex disorder than UC. Additionally, CD patients report a poorer quality of life and more anxiety symptoms than UC patients [49,50]. Therefore, it is important that UC and CD patients are distributed evenly in the experimental group and the waiting list control group.

In sum, there is a compelling need to enhance the quality of life of patients with IBD, especially in patients with a low level quality of life. CBT may be the most promising intervention given its empirical status over 5 decades [12,27]. It is expected to enhance the quality of life of IBD patients. Poor quality of life is not only a consequence of the disease but may in itself be a causal factor. It may induce a higher level of symptom severity, more reporting of unexplained physical symptoms and poorer treatment adherence. If found feasible and effective, this illness-oriented CBT is a first step to enhance poor quality of life in patients with IBD and, possibly, other gastroenterological diseases.

### Ethical considerations

The current study protocol was approved by the MEC of the AMC Amsterdam and confirmed by the institutional ethics review committees from the participating medical centers (i.e. Flevo Hospital, Slotervaart Hospital, VUmc).
